### Family-centered care program (FamilieNetz)

Following the increased knowledge about the adverse consequences of preterm birth on child and family, but also on the healthcare system, different psychosocial interventions for parents of preterm infants have been developed with the aim to improve the early parent-child-relationship and reduce parental stress [30–35]. However, existing interventions in Germany are not standardized and have not been evaluated rigorously, making it difficult to draw firm conclusions on their preventive effects [36–38].

A novel support and training program for families of sick newborns and preterm infants (FamilieNetz) was developed and introduced in clinical routine at the Department of Neonatology and Pediatric Intensive Care at the University Hospital Carl Gustav Carus, Dresden in 2009. The comprehensive program consists of different interventions, including parent counseling, parent education and discharge planning. Its philosophy focuses on empowering parents in primary caregiving for their child and involving them in daily routine as early as possible by giving them psychological and social-medical support during the initial hospital stay [39].

Single components of the intervention program have been evaluated and as a consequence health insurance companies in Saxony are compensating it in part since 2012. In a next step, the program shall be introduced into other perinatal centers in Saxony and later in Germany as well. However, prior to the introduction, a comprehensive evaluation of the whole multiple component approach is required, in accordance with the principles of evidence-based healthcare.

In order to address the issues outlined above, the study EcoCare-PIn will examine the following research questions:What are the short- and long-term consequences of preterm birth with regard to parental stress, parent-child relationship, family and child quality of life, child development, and healthcare utilization including costs?Does early family-centered psychosocial care prevent the hypothesized negative consequences of preterm birth on parental stress, parent-child relationship, family and child quality of life, child development, and healthcare utilization including costs?

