### Design and recruitment

The study is based on pseudonymized *administrative outpatient and inpatient data* of all children born in Saxony between January 1^st^, 2007 and December 31^st^, 2013 with health insurance at the AOK PLUS. The whole cohort of newborns will include almost 140,000 children, with approximately 1,000 VLBW- and 5,500 LBW-children among them. A broad set of insurance data will be provided and analyzed within this study, including birth weight (classified into <1,500 g (VLBW), 1,500–2,499 g (LBW) and ≥2,500 g (controls)), selected sociodemographic characteristics of children (age, sex, first three digits of ZIP code), diagnoses (ICD-10 codes), diagnosis related billing information (DRG-codes), prescriptions (PZN-codes, ATC-codes, cost), medical procedures (OPS-codes), claim codes for outpatient services and procedures (EBM-codes) and data of healthcare providers (discipline, first three digits of ZIP code) [42]. Based upon these pseudonymized administrative data, we will investigate and compare VLBW-, LBW- and control children with regard to mental and physical development, healthcare utilization and cost from birth through December 31^st^, 2013.

To enable further analyses, additional *primary data* will be collected on a subgroup of the described cohort of children. With support from the AOK PLUS, parents or legal caregivers from all preterm born children and parents/legal caregivers of a matched sample of 10,000 control children will be approached via postal questionnaires. Control children for the primary data collection will be selected via frequency matching according to birth year, sex and administrative district.

The questionnaire will cover information on parental stress, parent-child relationship, child’s physical and mental development (including school performance), quality of life of children, family quality of life, sociodemographic characteristics of parents, and exposure to psychosocial care in the neonatal period. These primary data will be linked to the administrative data on an individual level.

Figure 2 provides a flow chart on the design of the study.

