### Statistical analysis

Multivariate binary or multinomial logistic regression models as well as multiple linear regression models will be used to analyze the effect of birth weight (differentiated into VLBW, LBW and birth weight ≥ 2,500 g) on the outcomes. Adjustment will be made for sex, year of birth and socioeconomic status. Modification of the presumed adverse short and long-term effects of preterm birth through early psychosocial care will be analyzed by modeling the exposure to such a program as predictor for parental stress, parent-child relationship, quality of life, child development, healthcare utilization and costs. Effect modification will be explored by including the corresponding interaction-terms in the regression models. With an expected response rate of 30 % and an expected power (1-β) of 80 %, effect sizes (Cohen’s f) of 0.045 or higher can be detected at a 5 % significance level in analyses with the linked dataset (see Fig. 4). For analyses based on the whole administrative data cohort, effect sizes (Cohen’s f) of 0.035 or higher can be detected with a power of 80 % at the 5 % significance level.

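### The plan names no neonatal illness or place-of-care covariate for the psychosocial-care effect, so question 2 is open to confounding of unknown size and direction

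*Protocol article*

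**What the plan says.** The Statistical analysis section of the Protocol article first sets out models for the "effect of birth weight (differentiated into VLBW, LBW and birth weight ≥ 2,500 g) on the outcomes". One adjustment sentence follows: "Adjustment will be made for sex, year of birth and socioeconomic status". The second research question is then to be answered by "modeling the exposure to such a program as predictor for parental stress, parent-child relationship, quality of life, child development, healthcare utilization and costs", and "Effect modification will be explored by including the corresponding interaction-terms in the regression models". No further covariate, restriction to eligible infants, propensity method or center term is given for this second analysis.

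The section on FamilieNetz describes who is exposed: it is "A novel support and training program for families of sick newborns and preterm infants", introduced in the "Department of Neonatology and Pediatric Intensive Care at the University Hospital Carl Gustav Carus, Dresden in 2009" and delivered during the initial hospital stay. Extension to other perinatal centers is a later step.

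Under Design and recruitment, controls (2,500 g or more) are frequency matched on birth year, sex and administrative district, with no neonatal-admission criterion. Exposure to psychosocial care comes from the parent questionnaire. The claims file supplies "diagnoses (ICD-10 codes), diagnosis related billing information (DRG-codes" among other fields, including OPS procedure codes.

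**The concern.** Receiving the program requires that a newborn was ill or preterm and was treated in a particular kind of unit. Neonatal illness and place of treatment plausibly also affect development, utilization, cost and parental stress. None of the three named adjustment variables measures either. Year of birth deals with the 2009 start but not with illness or center, and birth weight in three classes captures illness only coarsely.

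The control group adds a second difficulty. Given the program's target group, exposed children of 2,500 g or more are mainly sick newborns, while unexposed controls are mostly healthy. Their exposure contrast is then largely sick versus healthy, and a birth weight × exposure term subtracts it from the preterm contrast.

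Question 2 is one of two primary questions. The article calls for a comprehensive evaluation before roll-out and expects the results to inform health policy. An estimate that mixes program effect with illness does not serve that purpose.

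**Working it through.** **The plan's own figure.** Questionnaires sent: 1,000 + 5,500 + 10,000 = 16,500. At 30 % response, N = 4,950. For an F test with 2 numerator degrees of freedom (three birth weight groups), noncentrality N·f² and 5 % significance, the detectable f at 80 % power is 0.0441. Power at the stated f = 0.045 is 81.6 %, so the figure reproduces. It describes the birth weight comparison and says nothing about the program effect.

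**Precision of the program contrast.** Preterm responders: 0.30 × 6,500 = 1,950. The detectable difference is 2.80 × √(1/n₁ + 1/n₀) in SD units. The exposed share is an assumption, since the article gives none.

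| Exposed share | Detectable difference, 1,950 preterm responders | VLBW only, 300 responders |
|---|---|---|
| 5 % | 0.29 | 0.74 |
| 10 % | 0.21 | 0.54 |
| 20 % | 0.16 | 0.40 |
| 30 % | 0.14 | 0.35 |

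**Simple bias calculation.** Bias = difference in illness prevalence (exposed minus unexposed) × illness effect. With an assumed difference of 20 to 30 percentage points and an effect of 0.3 to 0.5 SD, it runs from 0.2 × 0.3 = 0.06 to 0.3 × 0.5 = 0.15 SD. With 10 % exposed (195 versus 1,755), the standard error is √(1/195 + 1/1755) = 0.0755. The bias is then 0.06/0.0755 = 0.8 to 0.15/0.0755 = 2.0 standard errors.

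**Main effect and interaction together.** Assume no true program effect and let higher outcomes be worse. Assumed inputs: sick share 5 % in controls, 40 % in LBW, 90 % in VLBW; exposure 30 % of sick and 0 % of healthy controls, 40 % of sick and 20 % of non-sick preterm infants; illness effect 0.2 or 0.4 SD.

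- Controls: all exposed are sick; sick share among unexposed = 0.05 × 0.7/(0.05 × 0.7 + 0.95) = 0.036. Difference 0.964; apparent program effect +0.19 or +0.39 SD.
- LBW: 0.16/0.28 − 0.24/0.72 = 0.571 − 0.333 = 0.238; apparent effect +0.05 or +0.10 SD.
- VLBW: 0.36/0.38 − 0.54/0.62 = 0.947 − 0.871 = 0.076; apparent effect +0.02 or +0.03 SD.
- Interaction against controls (preterm effect minus control effect): LBW −0.15 or −0.29 SD; VLBW −0.18 or −0.36 SD.

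A simulation of 400,000 children with these inputs agrees up to sampling error: interactions of −0.17 to −0.35 SD, and all program terms within about 0.03 SD of zero once illness is in the model. The program thus looks mildly harmful within the preterm groups and protective in the interaction, although it does nothing. If some healthy controls also report psychosocial care, the control contrast and hence the interaction bias shrink.

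**Precision of interactions.** Assume 10 % of preterm and 1 % of control responders exposed, with 0.30 × 10,000 = 3,000 control responders.

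- Preterm versus control: 2.80 × √(1/195 + 1/1755 + 1/30 + 1/2970) = 0.56 SD.
- VLBW versus LBW (30 versus 270, 165 versus 1,485): 2.80 × √(1/30 + 1/270 + 1/165 + 1/1485) = 0.59 SD.

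**The case against.** The adjustment sentence directly follows the birth weight model, and the program model comes afterwards with no list of its own. A journal article may leave a second covariate set to the full plan. The interaction's reference level is not stated either, and effect modification is only to be explored. This stands as a limit: applying the three variables to the program model, and taking controls as reference, are natural readings but inferences. What remains is that the article names a set, gives no other, and does not name the illness data it obtains.

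A reader might infer that the interaction answers the wrong question or is invalid in itself. The documents do not support that. The Hypotheses section says that early intervention modifies the consequences of preterm birth, and a birth weight × exposure term translates this directly. A model with main effects and product terms also yields the effects within VLBW and within LBW. The weakness is that exposed and unexposed controls are not comparable.

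A reader might also infer that the bias runs against the program. The article does not say that sicker preterm infants were preferentially exposed. In a routine-care program at one department, exposure depends partly on hospital and birth year. The illustration itself gives opposite signs for the main effect and the interaction.

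It is fair, too, that every magnitude rests on assumptions and that a bias of 0.06 to 0.15 SD lies mostly below the detectable differences. That does not make it harmless, since it can still reach about two standard errors. Finally, replacing the control-referenced interaction by a VLBW-by-LBW one gains no precision (0.59 against 0.56 SD).

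**Conclusion.** The point holds in this form. The plan names only sex, year of birth and socioeconomic status, while exposure to the program it describes depends on neonatal illness and place of care. The program effect, and any interaction that takes the controls as reference, is therefore open to confounding that the named variables cannot remove.

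The documents do not fix the size or direction. Under the assumptions shown, the bias is 0.02 to 0.15 SD within preterm infants and 0.15 to 0.36 SD in the interactions, possibly with opposite signs. If the questionnaire's exposure item covers psychosocial care in any neonatal unit, dependence on a single center weakens, but the link with illness remains. The conclusion rests on reading the single adjustment set as applying to question 2, because no other is given. It does not require the control-by-exposed cell to be empty, since sick newborns of 2,500 g or more can be exposed.

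**What to change.** Make the main analysis of question 2 a comparison of exposed with unexposed children among infants eligible for the program: those below 2,500 g, or those admitted to a neonatal unit. Adjust, by covariates or a propensity score fixed in advance, for birth weight class and for neonatal diagnoses and procedures coded at or soon after birth, in addition to the variables already named. Codes from that early window are preferable to length of stay, which the program's discharge planning could itself change.

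Add region or provider by three-digit ZIP code as a proxy for center, since no center identifier is listed. Use the P07 subclass and multiple birth where they can be derived. According to Data preparation, P07.12 is the only five-digit P07 code assigned to LBW, so the subclass is informative only within VLBW. Multiple birth is not listed as a field.

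Keep these severity covariates out of question 1, where neonatal illness lies on the path from preterm birth to the outcome. Label any interaction with birth weight group as exploratory and imprecise, whichever groups it compares.

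The cost is some coding of claims variables already obtained and a few degrees of freedom. The core adjustment needs no new data. Illness that the codes do not capture remains a limitation to report.

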**Fig. 4 Fig4:**
[figure not shown]
Detectable effect sizes (Cohen’s f^2^) in analyses with the linked dataset depending on expected power

In an administrative data based cohort study the quality of data depends on the quality of documentation in care as well as on the quality of data recording by AOK PLUS [47]. Missing data in questionnaires (primary data collection) will be handled by methods of imputation or partial imputation if recommended in the test manuals. Statistical analyses will be conducted using the programmes STATA and SPSS.

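### The whole-cohort detectable effect (f = 0.035) cannot come from the same test and definition as the linked-dataset figure (f = 0.045); on that basis about 140,000 children detect f of about 0.008

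*Protocol article*

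**What the plan says.** The protocol article gives its power figures in two sentences of the Statistical analysis section. For the survey linked to claims data, at 30 % expected response and 80 % power, "effect sizes (Cohen’s f) of 0.045 or higher can be detected at a 5 % significance level in analyses with the linked dataset". For the claims data alone, "For analyses based on the whole administrative data cohort, effect sizes (Cohen’s f) of 0.035 or higher can be detected", again "with a power of 80 % at the 5 % significance level". Neither sentence names the test, the numerator degrees of freedom or the N.

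The sample sizes stand under Design and recruitment: "The whole cohort of newborns will include almost 140,000 children, with approximately 1,000 VLBW- and 5,500 LBW-children among them". All preterm children plus 10,000 matched controls are to be approached by post. The exposure has three birth-weight levels.

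The first sentence refers to Fig. 4, whose caption reads: "Detectable effect sizes (Cohen’s f^2^) in analyses with the linked dataset depending on expected power". The text uses f; the caption uses f².

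**The concern.** Moving from a 30 % survey to the full birth cohort multiplies the sample by about 28 (140,000 / 4,950), yet the stated detectable effect falls only from 0.045 to 0.035. For a fixed test, the detectable f shrinks with the square root of N, so a much larger drop is expected. These are the only power figures in the article. As printed, they suggest that the full claims cohort adds little sensitivity to the survey, which misrepresents a main strength of the design.

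**Working it through.** **Inputs.** From Design and recruitment: about 1,000 VLBW, 5,500 LBW and almost 140,000 children in all, hence about 140,000 − 6,500 = 133,500 controls; 10,000 controls approached. From Statistical analysis: 30 % response, 80 % power, 5 % alpha, three birth-weight groups. Assumptions: a three-group F test (df1 = 2), and uniform response across groups.

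**Method.** Noncentral F with noncentrality λ = N·f². At 80 % power, 5 % alpha and df1 = 2, λ is about 9.64, so detectable f = √(9.64 / N).

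**Step 1, linked dataset.** Approached: 1,000 + 5,500 + 10,000 = 16,500. Responders: 0.30 × 16,500 = 4,950 (300 / 1,650 / 3,000). Detectable f = √(9.64 / 4,950) = 0.0441. Power at f = 0.045 is 81.6 %. The stated 0.045 reproduces.

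**Step 2, whole cohort, same test.** Detectable f = √(9.635 / 140,000) = 0.0083. Power at f = 0.035 is effectively 100 %. The stated value is 0.035 / 0.0083 = 4.2 times larger. It corresponds to N of about 7,870 with df1 = 2, or about 6,410 with df1 = 1.

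**Step 3, numerator degrees of freedom.** At N = 140,000 the detectable f is:

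| df1 | detectable f |
|---|---|
| 1 | 0.0075 |
| 2 | 0.0083 |
| 10 | 0.0108 |
| 20 | 0.0122 |
| 1,000 | 0.0289 |
| 3,000 | 0.0378 |

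Reaching 0.035 would take between 1,000 and 3,000 numerator degrees of freedom.

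**Step 4, a bound that does not need df1.** Cohort group sizes divided by linked group sizes are 1,000/300 = 3.33, 5,500/1,650 = 3.33 and 133,500/3,000 = 44.5. Every group is at least 1/0.3 times its linked counterpart. For the same test and the same pattern of means, the detectable effect in the cohort is therefore at most √0.3 = 0.548 of the linked one: 0.548 × 0.045 = 0.025. The stated ratio is 0.035 / 0.045 = 0.78.

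**Step 5, where 0.035 could come from.** Two-sample Cohen's d = 2.80 × √(1/n1 + 1/n2).
- Preterm versus control, cohort: 2.80 × √(1/6,500 + 1/133,500) = 0.0356. This matches 0.035, but it is a d. The linked counterpart is 2.80 × √(1/1,950 + 1/3,000) = 0.0815, not 0.045.
- A single-df test in the 6,500 preterm children alone gives f = 0.0348, but that is not the whole cohort.
- If f is defined on equally weighted group means, the answer depends on the pattern of means. With VLBW and LBW equally affected, the cohort/linked pair is 0.019 / 0.043; with a 4:1 deficit, 0.0365 / 0.076; with only VLBW affected, 0.046 / 0.087. None of these gives 0.035 with 0.045.

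**Step 6, scale.** The linked detectable f² is 0.0441² = 0.0019, about 0.002, and √0.002 = 0.0447. Read as f² values, 0.045 and 0.035 would need only about 217 and 278 children. The printed numbers fit f.

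**The case against.** The strongest defence is that the article never says that both figures use one test. It lists binary, multinomial and linear models, and the claims analyses have different outcomes from the survey. So 0.035 may be a sound number for another measure, such as d for preterm versus control, under the wrong label. That stands, and it means 0.008 is the right replacement only if f keeps the meaning that reproduces the linked figure. It does not rescue the sentence, which calls 0.035 a Cohen's f for the whole cohort.

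It is also fair that an effect of 0.035 or more is indeed detectable with 140,000 children. The error understates sensitivity, and the sample size does not depend on it, because all insured births enter and all preterm families are approached.

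Three stronger readings are tempting and are not supported:
- A reader might infer that the survey is underpowered, because an equal-weight definition of f can bring the cohort value near 0.035 and then raises the linked value. That definition is a guess, and its linked detectable f runs from 0.043 to 0.087 with the pattern of means. Under the ordinary definition 0.045 has 81.6 % power.
- A reader might infer that the Fig. 4 caption is mislabelled. The figure is not available for this review. An axis in f² reading about 0.002 agrees with f = 0.045 in the text, so f and f² may both be correct.
- A reader might infer that 0.045 fails for the psychosocial-care question because that question uses preterm responders only. The article does not say so: it models exposure as a predictor with interaction terms, describes the programme as serving sick newborns as well as preterm infants, and asks about exposure in the questionnaire, which also goes to controls.

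**Conclusion.** The point holds as a reporting error in one sentence. The linked figure of 0.045 is correct for a three-group test on 4,950 children. The whole-cohort figure of 0.035 is about four times the value that the same test gives (0.0083), and it exceeds the ceiling of about 0.025 that applies to any shared test and definition. Either the number or its label is wrong; the article does not allow one to say which.

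The value of 0.0083 assumes df1 = 2 and N of about 140,000; the ceiling assumes uniform response. The discrepancy runs in the conservative direction. It does not show a loss of power and does not call for a change in design.

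**What to change.** Choose one of two corrections to the whole-cohort sentence:
- keep f as defined for the linked figure, and restate the cohort value as about 0.008; or
- if 0.035 is another measure, such as d for 6,500 preterm versus 133,500 control children, label it so and name the test and N. For comparability, the linked d would then be given as about 0.08.

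In either case, state the test and N behind each figure. Check the scale plotted in Fig. 4 against the text, and either use one scale in both or state the conversion (f² of about 0.002 corresponds to f of about 0.045). The cost is a few words of text and possibly of the caption. Sample size, data collection and analysis are unaffected.

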**Fig. 4 Fig4:**
[figure not shown]
Detectable effect sizes (Cohen’s f^2^) in analyses with the linked dataset depending on expected power

In an administrative data based cohort study the quality of data depends on the quality of documentation in care as well as on the quality of data recording by AOK PLUS [47]. Missing data in questionnaires (primary data collection) will be handled by methods of imputation or partial imputation if recommended in the test manuals. Statistical analyses will be conducted using the programmes STATA and SPSS.

